### Randomization

Eligible patients will be assigned into two groups (*n* = 40 in each group) of the cornelian cherry fruit extract and the placebo group using the randomization method, which will be performed using the Random Allocation Software [56]. The participants will be also stratified based on age, gender, BMI, and severity of fatty liver (fatty liver grade 1, 2, 3).

### Intervention

The target daily dose of 320 320 mg.d^− 1^ of total anthocyanin will be administered for 12 weeks [42]; with the required daily intake of extract adjusted in accordance with the total anthocyanin content measured in the extract. Moreover, the total anthocyanin content in the extract will be measured in distinct intervals during the trial (on days 1, 6, 12, 20, and after 6 months). If it is required, we will adjust the amount of consumed extract based on its total anthocyanin content.

The control group will also receive the placebo, matched with the extract in terms of appearance, taste, color, and texture (but without any anthocyanins) for 12 weeks. The participants will be asked to keep the intervention and placebo, which are presented as liquid in the refrigerator to ensure food safety.

In the current double-blind randomized clinical trial, the cornelian cherry extract and the placebo will be packed in containers with the same color, shape, and size, so that they cannot be identifiable by the patients or administrators. A person out of research, who does not know about the details of study, will be asked to label the bottles containing the extract or placebo as A or B, the contents of these bottles should be consumed in one month by participants. This person will be asked to inform the researchers about his/her labeling selection at the end of study. We will also ask the participants to give back their bottles (empty or not) at the end of each month and receive the next bottles until the end of study. At the end of intervention, the remaining contents of bottles will be recorded for each participant. Moreover, regular consumption of the extract or placebo will be checked by contacting the patients during the survey. At the end of the trial, the consumed amounts of extract or placebo will be estimated considering the remaining contents of the bottles for each participant. In the case that a patient in each group consumed less than 80% of the administered extract or placebo, his/her data will not be analyzed at the end of the study.

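### With one shared label per arm and a mid-trial change in amount described for the extract only, a one-sided change or a single disclosure could reveal every participant's allocation

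*Protocol article*

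**What the plan says.** All of the relevant text stands in the Intervention section of the protocol article.

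- **Labelling.** The labeller is described as "A person out of research, who does not know about the details of study". This person "will be asked to label the bottles containing the extract or placebo as A or B". There are therefore two codes for the whole trial, one per arm.
- **Key.** "This person will be asked to inform the researchers about his/her labeling selection at the end of study".
- **Assay.** The anthocyanin content of the extract "will be measured in distinct intervals during the trial (on days 1, 6, 12, 20, and after 6 months".
- **Adjustment.** "If it is required, we will adjust the amount of consumed extract based on its total anthocyanin content". The subject of the sentence is the research team.
- **Placebo.** It is "matched with the extract in terms of appearance, taste, color, and texture (but without any anthocyanins) for 12 weeks". Amount is not on that list.
- **Supply.** Participants "give back their bottles (empty or not) at the end of each month and receive the next bottles until the end of study".
- **Aim of the blind.** Containers share colour, shape and size "so that they cannot be identifiable by the patients or administrators".

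**The concern.** The team that is to change the amount of extract is the team that is not to know which label is extract. The key-holder is someone outside the research who is not told its details, and no other unblinded role is named. As written, nobody has both the knowledge and the task.

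The shared code then determines how far any leak spreads. If the amount changes under one label and not the other, that label is extract for every participant who carries it, and the other label is placebo.

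If the blind were lost, some parts of the trial would be exposed:

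- hepatic steatosis and fibrosis, which a gastroenterologist measures by transient elastography (Primary outcomes);
- food records and the physical activity questionnaire, which are self-reported (Data collection);
- contacts with participants about adherence (Intervention);
- removal from the analysis of participants who come under some other medical treatment during the study (Study population), which can involve judgement.

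**Working it through.** The plan gives no figure on this point, so the check is mainly a reading of the steps against each other. The only count needed is the group size in the Randomization section, 40 per arm.

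**1. Who can carry out the adjustment?** Changing the extract alone requires knowing which label is extract. The researchers do not know this until the end. The labeller does know, but is given neither the assay results nor the task. The two steps do not fit together unless the same change goes to both labels or a further role is added. The text states neither.

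**2. What does a one-sided change reveal?** An observer needs three things: sight of both labels, sight that only one changed, and the knowledge that it is the extract that is adjusted. Staff who exchange bottles and record returned volumes could have all three. A participant sees only their own bottle and learns little from a change in amount by itself.

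**3. How far does one leak spread?**

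| Coding | Participants revealed by one disclosure |
|---|---|
| Two shared codes (as written) | 40 + 40 = 80 of 80 |
| Participant-specific codes | 1 of 80 |

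The first row does not depend on an adjustment. Learning the content of one bottle for any reason is enough.

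**4. When could a change fall?** The zero point of the assay days is not stated.

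- If they count from first intake, days 6, 12 and 20 come before the first monthly bottle exchange. A change then could not wait for new bottles and would need an instruction to participants already holding theirs.
- If they count from preparation of the extract, some may precede dosing. The last point, after 6 months, lies beyond a 12-week intake period and fits this reading better. Table 1 also places standardisation in month 5 and the intervention in months 12 to 14. Against this, the sentence places the measurements during the trial.

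**5. Which outcomes are exposed?** Primary outcomes lists eight measures.

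- Six are auto-analyser or ELISA results: ALT, AST, TNF-α, MDA, adiponectin and CK-18 M30.
- Two are performed by an operator: steatosis and fibrosis by elastography.

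The six, including ALT on which the sample size rests, are less open to assessor bias, although a change in participants' behaviour could still reach them.

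**6. Adherence.** The 80% intake rule is set against the amount administered. An extract-only change would give the two labels different denominators, which is another place where the arms could be told apart.

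**The case against.** A reader might infer that the procedure cannot be run without unblinding everyone. The article does not support that, for these reasons:

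- **The adjustment is conditional.** If the anthocyanin content stays stable, nothing is changed and nothing is revealed by this route.
- **A parallel placebo change is not excluded.** The sentence may name the extract simply because the placebo contains no anthocyanin. Giving both labels the same new amount would need no key, and a later batch could be altered before it is labelled.
- **The assay itself needs no key.** It can be run on unlabelled stock.
- **Most primary measures are laboratory results**, and the 80% rule is numerical, so the room for bias is narrower than a general loss of blinding suggests.
- **A two-code scheme is not in itself an error or a contradiction.** Nor does the taste matching allow one to assume that participants could identify the product by comparing bottles.

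All of this stands. It could also be said that dispensing detail belongs in a full protocol and not in an article. That is fair as to the mere absence of a placebo instruction. It does not answer what the article does state: one code per arm, a key withheld from the team, and an adjustment by that team worded for one arm. Nor do the blind-preserving routes appear in the text. Altering a batch before labelling also protects the blind only if the two products still match in amount.

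**Conclusion.** The point holds as a risk created by the stated procedure. Under the two-code scheme, an adjustment made to the extract alone could reveal the allocation of all 80 participants to anyone who saw that only one label changed and knew the reason. A single disclosure would do the same without any adjustment. With participant-specific codes, one disclosure reveals 1 of 80.

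The first statement assumes that an adjustment proves necessary and that placebo is not changed with it. The second assumes only the coding scheme as written. How likely either event is cannot be estimated from the article.

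The consequences fall mainly on the two elastography measures, the self-reported diet and activity data, and the exclusions after randomisation that call for judgement. The six laboratory measures are less exposed. The labelling should be changed and the adjustment and blinding sentences reconciled. Nothing here bears on the dose or on whether or when an adjustment is warranted.

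**What to change.** 1. Replace the two labels with participant-specific bottle codes generated from the randomisation list. The key should be held by someone independent of enrolment and outcome assessment.
2. Reconcile the adjustment sentence with the blinding sentence: assay results go to the key-holder, and any change in amount is issued identically and simultaneously to both arms, so that the researchers never need the key.
3. State the zero point of the assay days, so that it is clear whether a change can fall between bottle exchanges.

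Cost: a labelling list, one revised protocol paragraph and slightly more labelling work. The present labeller is defined as not knowing the study's details, so that person, or another key-holder, would have to be briefed and remain available throughout the trial.

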### Data collection

Data on patients’ demographic information, history of diseases, and consumption of medications or supplementations will be collected using a general questionnaire at the beginning of the research.

Participants’ dietary intakes will be evaluated using a three-day food record (2 week days and 1 weekend day) at the baseline and at the end of trial. Then, to estimate the total energy and macronutrients’ intakes, Nut IV (the Hearst Corporation, San Bruno, CA) will be used. Moreover, in order to evaluate the patients’ physical activity levels, the short form of International Physical Activity Questionnaire (IPAQ) will be administered at the beginning and the end of survey. Meanwhile, anthropometric parameters (e.g., weight, height, Body Mass Index (BMI), and waist and hip circumference) will be measured with minimal clothing and without shoes at the baseline and at the end of study. Body weight will be assessed by a seca scale with an accuracy of 100 g. Height will be measured in a relaxed position with the accuracy of 0.5 cm by a seca stadiometer. Then, BMI will be calculated after dividing the body weight (kg) by the square of height (m). Waist circumference will be also measured at the midway between the lowest ribs and the iliac crest. Moreover, hip circumference will be measured over the largest part of the buttocks.

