### Study population

Patients with NAFLD will be selected based on the inclusion and exclusion criteria from gastroenterology clinics affiliated to Diabetes Research Center and Shahid Sadoughi University of Medical Sciences, Yazd, Iran. The inclusion criteria will be having 25–65 years of age; ALT levels of higher than 30 U/L in men and higher than 19 U/L in women; diagnosis of the disease by a gastroenterologist; and grade 1, 2, and 3 fatty liver. Furthermore, patients should be residents of Yazd city and will be required to sign the written consent forms to participate in the research. In the current research, nonalcoholic steatohepatitis (NASH) will be defined based on the guidelines of American Gastroenterological Association and American Association for the Study of Liver Diseases [54]. According to this guideline, NASH is defined as the presence of hepatic steatosis proved by ultrasonography or inflammation with hepatocyte injury (ballooning) with or without fibrosis [54]. Moreover, NAFLD will be diagnosed by ultrasonography based on following criteria: an increase in hepatic echogenicity via renal echogenicity as a reference, presence of enhancement and lack of differentiation of periportal, and bile duct walls reinforcement due to great hyperechogenicity of the parenchyma [55]. Exclusion criteria will include: having any history of diseases such as cirrhosis, viral hepatitis, cardiovascular disease, diabetes, Wilson, and cancer; taking medications including corticosteroids, non-steroidal anti-inflammatory drugs, hypoglycemic agents, or any medicines that affect the blood glucose, tamoxifen, sodium valproate, methotrexate, amiodarone, anti-retroviral agents for HIV, probiotics; consuming any medicine or supplement that affect liver function as well as supplements with antioxidant and anti-inflammatory properties (such as vitamin D, vitamin E, omega-3, resveratrol) one month before the study; following a special diet one month before the study; being pregnant and breastfeeding; and consuming alcohol. We will also ask the patients to not consume the medicines in exclusion criteria list during the study. Moreover, data of the patients with any of the following conditions will not be analyzed at the end of study: patients who take less than 80% of the administered extract or placebo as well as participants who are under a special treatment due to a specific medical reason during the study.

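### Patients under special treatment during the study are dropped from the analysis, but the only medication and supplement record the protocol article describes is taken at the start

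*Protocol article*

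**What the plan says.** All references are to the protocol article.

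- **Data collection, medicines and supplements.** A general questionnaire, which also covers demographics and disease history, takes this information once: "consumption of medications or supplementations will be collected using a general questionnaire at the beginning of the research".
- **Data collection, neighbouring items.** Diet is recorded by a "three-day food record (2 week days and 1 weekend day) at the baseline and at the end of trial", used "to estimate the total energy and macronutrients’ intakes". The physical activity questionnaire "will be administered at the beginning and the end of survey". Anthropometry is also measured at both time points.
- **Study population, request during follow-up.** "We will also ask the patients to not consume the medicines in exclusion criteria list during the study".
- **Study population, removal from the analysis.** Two groups are left out at the end: patients who took less than 80% of their product, and "participants who are under a special treatment due to a specific medical reason during the study".
- **Intervention, contacts during follow-up.** "We will also ask the participants to give back their bottles (empty or not) at the end of each month". In addition, "regular consumption of the extract or placebo will be checked by contacting the patients during the survey". The contents left in the bottles are recorded and used to estimate how much was consumed.

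**The concern.** Two in-study conditions depend on knowing what patients took after randomisation: the request to avoid listed medicines, and the removal of patients under special treatment. A questionnaire completed at entry cannot show treatment begun during the 12 weeks.

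Two things are at stake. First, the removal rule acts after randomisation. Without a described way of finding the patients it applies to, it may be applied unevenly from patient to patient. Second, the entry criteria themselves treat medicines affecting liver function, and antioxidant or anti-inflammatory supplements, as reasons not to enrol. The same products taken during follow-up could affect ALT, TNF-α and MDA, all primary outcomes. If their use is not recorded, no sensitivity analysis can show whether it mattered.

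**Working it through.** **1. The two removal rules side by side**

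| Rule (Study population) | Information needed | Source the article describes |
|---|---|---|
| Intake below 80% | Amount of product consumed | Monthly bottle return, recorded remaining contents, contacts about intake (Intervention) |
| Special treatment during the study | Treatment begun or taken in weeks 1 to 12 | None; the medication questionnaire is dated to the start (Data collection) |

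The request to avoid listed medicines is in the same position as the second row. The end-of-trial food record does not fill the gap: it covers three days, and its stated use is energy and macronutrients.

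**2. The plan's own sample size**

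Inputs from Sample size: difference 16 and SD 24 (percentage points of ALT change, as I read the wording), α = 0.05 (two-sided assumed, since sidedness is not stated), power 80%.

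n per arm = 2 × (1.960 + 0.842)² × 24² / 16² = 35.3, rounded up to 36. Allowing for 10% loss, 36 / 0.90 = 40. Both match the article. Two-sample t-test power at 36 per arm is 79.7% (the normal approximation gives 80.7%).

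**3. What unrecorded use might do, on assumed figures**

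The article gives no rate of in-study use. I assume that a share p of 5%, 10% or 15% takes a product with the full 16-point effect on ALT.

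*Placebo arm only (worst case).* The expected difference becomes 16 × (1 − p), with the SD held at 24.

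*Equal use in both arms, additive effect.* The expected difference stays at 16. The variance in each arm becomes 24² + p(1 − p) × 16².

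| p | Placebo only: difference | Placebo only: power | Equal use: variance | Equal use: SD | Equal use: power |
|---|---|---|---|---|---|
| 5% | 15.2 | 75.5% | 576 + 12.16 = 588.16 | 24.25 | 78.8% |
| 10% | 14.4 | 70.9% | 576 + 23.04 = 599.04 | 24.48 | 78.1% |
| 15% | 13.6 | 66.0% | 576 + 32.64 = 608.64 | 24.67 | 77.4% |

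All powers are for the two-sample t-test at 36 per arm, against 79.7% with no such use.

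**The case against.** The strongest reply is that this is a condensed article. It dates one intake questionnaire to the start; it does not say that medicines are never asked about again. A rule on in-study treatment presupposes some way of learning of it, and that detail could sit in a case report form or the full protocol. Patients are also seen monthly for bottles, contacted in between, and examined by a gastroenterologist at the end.

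Much of this stands. A reader might infer that medication is certainly recorded only once, that in-study treatment would surface only by chance, or that contamination can never be measured. The article does not establish any of these: they rest partly on its silence, and the contacts give real occasions to ask.

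What does not stand is that the matter is merely left out. The article states a timing for this item and gives its neighbours two time points. It describes the in-study contacts for product intake only. It gives one removal rule a measurement and the other none. An analysis plan cannot use data that were not collected.

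A second reply is that double blinding makes uneven use or reporting between the arms less likely. That is fair. The article shows no mechanism for a difference between arms, so a differential bias is possible but not demonstrated.

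**Conclusion.** The point holds as a gap in the data collection as described: the rule removing patients for in-study treatment has no stated systematic source, and in-study use of liver-active or antioxidant products could not be examined from the records the article lists. This conclusion comes from comparing the sections and does not depend on any power figure.

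The size of any effect is unknown. A reader might take a fall in power to 66% as the consequence. The document does not support that: it needs 15% use, in the placebo arm only, of a product as strong as the effect the trial is powered to detect. With equal use, the same rates cost about 1 to 2 percentage points. The rates, the effect size and any imbalance are all assumptions.

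The point is worth acting on because the change is cheap during follow-up, and use that was not recorded then cannot be recovered reliably afterwards.

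**What to change.** 1. Ask the same short set of medication and supplement questions in both arms at each monthly bottle return and at week 12, and complete this before the A/B code is released.
2. Keep all randomised patients who report such treatment in the primary analysis instead of dropping them, and use the records for a sensitivity analysis. This step is needed separately, because better recording alone does not cure a post-randomisation removal.
3. State in the protocol what counts as special treatment, so that patients are classified in the same way in both arms for that sensitivity analysis.

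The cost is a few extra questions at contacts that already take place, and slightly more data entry. The sample size does not need to change on this account.

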### Outcomes measurements

At the baseline and at the end of the research, 10 ml of blood sample will be taken from each participant after 10–12 h of overnight fasting for biochemical analyses.

#### Primary outcomes

At the baseline and at the end of trial, serum concentrations of Alanine aminotransferase (ALT) and Aspartate aminotransferase (AST) will be measured with an auto-analyzer. Serum levels of TNF-α, MDA, adiponectin, and CK-18 M30 will be also determined by Enzyme-linked immunosorbent assay (ELISA).

Furthermore, hepatic steatosis and liver fibrosis will be examined using transient elastography by a gastroenterologist at the baseline and at the end of the survey. Evaluation will be conducted while patients are lying in a dorsal decubitus position with their right arm in maximum abduction [57].

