
## Methods

### Design and aim study

This double-blind randomized parallel clinical trial will be carried out at the Department of nutrition, School of Public Health, Shahid Sadoughi University of Medical Sciences, Yazd, Iran. The main aim of this research is to investigate the effect of a 12-week supplementation with total anthocyanin-base standardized cornelian cherry fruit extract on liver function (Serum levels of AST, ALT and CK-18 M30; steatosis and fibrosis of liver), TNF-α, MDA, and adiponectin in patients with NAFLD. (Fig. 1 and Table 1). Moreover, serum concentrations of glucose, total TC, HDL-C, LDL-C, TG, insulin, and insulin resistance will be assessed as the secondary outcomes.

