### Sample size

To estimate the sample size, we considered 95% confidence interval; 80% power (α = 0.05 and β = 0.2); the changes of ALT levels in intervention group compared with the control group, and S = 24% to achieved the significance level of 16% in both study groups according to the study by Zhang et al. [42]. Therefore, the sample size was calculated as *n* = 36 for each group. Eventually, 40 patients will be recruited for each group considering the possible 10% loss.

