### Statistical analysis

Data analysis will be conducted using SPSS version 24 (SPSS Inc., Chicago, IL, USA). The normality of variables will be evaluated using Kolmogorov- Smirnov test. Qualitative and quantitative variables will be presented as numbers (percentages) and mean ± Standard Deviation (SD) or medians with interquartile ranges, respectively. Then, the Chi-Squared test will be used to compare the qualitative variables between two groups. In addition, the variables with normal distribution will be compared between and within the groups using the independent sample t-test and the paired sample t-test, respectively. However, in order to compare the variables with non-normal distribution between and within the groups, Mann-Whitney test and Wilcoxon test will be applied, respectively. To control the confounding variables, analysis of covariance (ANCOVA) will be used to examine the differences in post-intervention values between the two groups while adjusting for the baseline values and covariates. A *p*-value of < 0.05 will be considered as the statistically significant level.

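### Eight outcomes are labelled primary under one 0.05 threshold, but the sample size is built on ALT alone; ALT should be named as the single primary outcome

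*Protocol article*

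**What the plan says.** All references are to the protocol article.

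- **Primary outcomes** names eight variables in three sentences. The first covers the two enzymes: "serum concentrations of Alanine aminotransferase (ALT) and Aspartate aminotransferase (AST) will be measured with an auto-analyzer". The second adds four further blood markers: "Serum levels of TNF-α, MDA, adiponectin, and CK-18 M30 will be also determined by Enzyme-linked immunosorbent assay (ELISA". The third adds the two elastography measures: "hepatic steatosis and liver fibrosis will be examined using transient elastography by a gastroenterologist". A separate Secondary outcomes section follows, so the primary label is a deliberate classification.
- **Design and aim study** gives the same eight as the main aim: "liver function (Serum levels of AST, ALT and CK-18 M30; steatosis and fibrosis of liver), TNF-α, MDA, and adiponectin in patients with NAFLD".
- **Sample size** uses one outcome: "the changes of ALT levels in intervention group compared with the control group, and S = 24% to achieved the significance level of 16" (in percent), with "80% power (α = 0.05 and β = 0.2". The result is 36 per group, raised to 40 for 10% loss.
- **Statistical analysis** closes with one general rule, that a p-value "of < 0.05 will be considered as the statistically significant level". It does not treat primary and secondary outcomes differently.

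**The concern.** The sections treat the trial's main question in two ways. The sample size treats ALT as the outcome that decides the trial. The outcome list and the aim give ALT no more weight than seven others. With one threshold for all and no stated success rule, the text lets a single nominal p-value among eight be presented as a positive primary result for the extract.

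Two things are at stake. The first is the error rate behind the main conclusion, which is not 5% on that reading. The second is power: it is stated for one primary outcome and unstated for the other seven. The choice also gets harder to make later, because ranking the outcomes after the results are known would not be credible, and dividing alpha among eight would use up the power that the calculation claims for ALT.

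**Working it through.** **Inputs from the article**
- Eight primary outcomes: ALT, AST (2); TNF-α, MDA, adiponectin, CK-18 M30 (4); steatosis, fibrosis (2).
- Threshold 0.05; power 0.80; 36 per group, 40 after 10% loss; 1:1 allocation.
- SD 24%. The 16% is worded as a significance level. It is read here as the difference to detect, because that reading reproduces the stated 36.

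**Assumptions, not in the article**
- Tests are two-sided.
- There is one between-group test per outcome.
- No outcome is truly affected (for the error rate).
- Success on any one outcome counts as a primary success.
- The eight test statistics share a common correlation ρ. For two-sided tests, reversing an outcome's direction (as for adiponectin) changes nothing.

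**Step 1. Reproduce the plan's own figure.**
n = 2 × [24 × (1.960 + 0.842) / 16]² = 35.3, rounded up to 36 per group. Then 36 / 0.9 = 40. Both stated figures are correct for ALT. A one-sided test would give 28, so two-sided is the reading that fits.

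**Step 2. Chance of at least one false positive, independent tests.**
1 − 0.95⁸ = 1 − 0.663 = 0.337.

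**Step 3. The same chance with correlated tests.**
With c = 1.96,
1 − ∫ [Φ((c − √ρ·u)/√(1−ρ)) − Φ((−c − √ρ·u)/√(1−ρ))]⁸ φ(u) du.

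| Assumed common ρ | Chance of ≥ 1 false positive |
|---|---|
| 0 | 33.7% |
| 0.2 | 31.9% |
| 0.3 | 30.0% |
| 0.5 | 25.0% |
| 0.7 | 19.1% |
| 0.8 | about 16% |
| 0.9 | 11.9% |

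A mixed pattern was also simulated, with ALT and AST at 0.8 and all other pairs at one value from 0.1 to 0.5. It gives about 32% falling to 24%.

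**Step 4. Effect on ALT power of dividing alpha by eight.**
Bonferroni level: 0.05 / 8 = 0.00625. Standardised difference: 16 / 24 = 0.667. Noncentrality at 36 per arm: 0.667 × √(36/2) = 2.83, with 70 degrees of freedom.

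| Method | Power at 0.05 | Power at 0.00625 |
|---|---|---|
| Noncentral t | 79.7% | 50.7% |
| Normal approximation | 80.7% | 53.7% |

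Restoring 80% at 0.00625 would take 58 per group by the normal formula, and 58 / 0.9 = 64.4, so 65 recruited per group against the planned 40.

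**The case against.** **The analysis plan may deal with multiplicity.** Adjustment procedures are often left to a document that is not shown here, and their absence from an article is not an error. That much stands. But this article itself fixes the primary list, the outcome behind the sample size and the threshold, and those three do not fit together. An unseen plan that divided alpha among the eight would undercut the stated power. One that promoted ALT would depart from the stated list. Either way this text needs changing.

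**The error rate depends on assumptions.** This also stands. A reader might infer that the trial's false positive risk simply is 25% to 34%. The documents do not support that: they give no correlations and no success rule, and a stronger common correlation gives a lower figure. If all eight had to succeed, the error rate would not be inflated at all. Power would then suffer instead: even with 80% power for each outcome and independence, 0.8⁸ = 16.8%. The article states no such rule.

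**Any correction costs the ALT power.** A reader might infer this too, but it holds only for methods that divide alpha, such as Bonferroni. Testing ALT first at the full 0.05 costs ALT nothing.

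**The trial is underpowered for the other seven.** This cannot be shown. Their power is unstated, which is not the same as low.

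**ALT need not be the one.** The Background presents elastography and the adipokine, inflammatory and oxidative markers as gaps in earlier trials, so a different structure could be defended. It would need its own success rule and sample size. Only ALT fits the calculation already made.

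**Conclusion.** The point holds as a conflict among stated items: eight primary outcomes, one 0.05 threshold, and a sample size that covers one of the eight. The sample size arithmetic is right for ALT.

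If no outcome is truly affected and any one success counts, the chance of at least one false positive primary result is 33.7% under independence, 25% at a common correlation of 0.5, 19% at 0.7 and 16% at 0.8. The correlations are assumed, so no single figure can be given. The risk is still more than twice 5% even at 0.9. Bonferroni over all eight would lower ALT power at 36 per arm from about 80% to about 51%.

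This needs correcting before results are seen, because it decides what may be claimed as the trial's main result. It does not extend to the glucose, lipid and insulin outcomes: nothing here shows a fault in their secondary status.

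**What to change.** - **Design and aim study** and **Primary outcomes**: name ALT at week 12 as the single primary outcome, compared between groups at two-sided 0.05. This matches the Sample size section and keeps its power.
- Move AST, CK-18 M30, steatosis, fibrosis, TNF-α, MDA and adiponectin to key secondary outcomes.
- **Statistical analysis**: state that these seven are tested formally only after ALT succeeds, either by Holm or in a fixed order written down now.
- **Secondary outcomes**: leave the outcomes listed there as secondary.
- **Abstract** and **Background**: bring the aim statements into line.

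The registry record was not available. Check whether it carries the same list of eight, and amend it if so.

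Cost: wording only, with no added patients, visits or assays. The downside is that seven outcomes lose the primary label, including the elastography measures that the Background presents as an advance on earlier trials.
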